### Study Procedures and Interventions

Within the control group, blood cardioplegia will be administered by means of a cold induction dose at 4-8 °C and a maintenance dose administered every 20 minutes. It will be dispensed via the anterograde or retrograde approach according to the protocol of the center.

Within the intervention group, del Nido cardioplegia will be administered according to the usual practice in a single dose of 1000 cc via the anterograde or retrograde approach according to the protocol of the center. Additional doses (550 mL) will be administered when spontaneous electrical activity appears or, in the case of periods of ischemia, longer than 90 minutes. Common clinical practice will not be modified in the remaining perioperative aspects.

### Outcome Measures

The main variables of the study will be the composite clinical variable *acute cardiovascular event* and the biochemical variable *maximum postoperative troponin value*.

The *acute cardiovascular event* variable will consist of one or several of the following events:

Early perioperative myocardial infarction: occurring during the first 72 hours after surgery and defined according to the criteria of the Task Force of the European Society of Cardiology, the American Heart Association, and the World Heart Federation.Prolonged low cardiac output: defined as the need to maintain support with two or more inotropic and/or other circulatory mechanical assistance devices—intra-aortic balloon counterpulsation (IABC) or extracorporeal membrane oxygenation (ECMO)—beyond the first 24 postoperative hours.Appearance of ventricular arrhythmias: ventricular tachycardia (VT) and ventricular fibrillation (VF) requiring electrical cardioversion in the first 24 postoperative hours.

To analyze the effect of cardioplegia on myocardial protection at a biochemical level, the level of troponins will be monitored upon arrival at the ICU and during the first 48 hours. Likewise, the maximum troponin peak will be collected during the first 48 postoperative hours.

Other secondary variables of efficacy and safety will be analyzed. Among the intraoperative variables, surgical times (ie, ischemia time and cardiopulmonary bypass times), the volume of cardioplegia solution administered and its route of administration, temperature, average blood pressure, and maximum blood glucose values, as well as the need for electrical cardioversion after aortic cross-clamp release, will be monitored.

Among the postoperative variables, the occurrence of atrial fibrillation will be registered, as well as the requirement for inotropic and mechanical pharmacological support, time to withdrawal, and the occurrence of clinical complications (ie, deterioration of ventricular function upon hospital discharge, surgical reintervention, prolonged mechanical ventilation, acute kidney injury, infectious complications, convulsive activity, or stroke). The need for ICU readmission, ICU and hospital length of stay, and mortality will also be noted.

Subgroup analyses will be carried out in four populations: elderly patients (over 80 years), patients undergoing prolonged cardiopulmonary bypass (longer than 120 minutes), patients with low ventricular ejection fraction (less than 30%), and patients subjected to coronary artery bypass grafting.

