#### Analyses

A description of the data from each group of the study and the total sample will be carried out. The properties of the original variables will be defined, and the aforementioned composite variables will be created. The main variable—*prolonged low cardiac output syndrome*—will be created from the following original variables: *presence of two or more inotropic agents at 24 hours of admission*, *mechanical support with IABC*, and/or *mechanical support with ECMO or other ventricular assistance*. The main composite variable—*acute cardiovascular event*—will be created from the following variables: *perioperative myocardial infarction*, *prolonged low cardiac output syndrome*, *prolonged vasoplegia*, and/or *VT or VF episodes in the first 24 hours*.

The quantitative variables shall be described through the mean (SD), median (IQR), 95% CI, and minimum and maximum values. Qualitative variables shall be presented as relative and absolute frequencies. To ensure the uniformity of the groups, a detailed analysis will be made by evaluating the association using the Pearson correlation coefficient and the *P* value by means of the Student-Fisher *t* test; correction for unequal variances for the quantitative variables, and the association with the odds ratio and the *P* value, will be obtained with chi-square tests for the categorical variables.

The raw effect of each type of cardioplegia on the acute cardiovascular event will be estimated using a logistic regression model.

Two populations will be defined through intention-to-treat analysis and by biological efficacy. The first population will include all the initially randomized subjects, including all those who leave the study due to noncompliance. The second population will include all those subjects who complete the study within the same group in which they were randomized. An intermediate safety analysis will be performed when approximately 50% of patients have been randomized.

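### Death is in neither definition of the primary composite, so a patient who dies before 24 h of pump failure on inotropes alone can be scored event-free

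*Protocol article*

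**What the plan says.** The article defines the primary clinical outcome, acute cardiovascular event, in two places.

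**Outcome Measures.** The "variable will consist of one or several of the following events", and three are given:
- "Early perioperative myocardial infarction: occurring during the first 72 hours after surgery";
- prolonged low cardiac output, "defined as the need to maintain support with two or more inotropic and/or other circulatory mechanical assistance devices", where that support continues "beyond the first 24 postoperative hours";
- ventricular tachycardia or fibrillation "requiring electrical cardioversion in the first 24 postoperative hours".

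Death is not among them. It appears only with the other postoperative variables: "The need for ICU readmission, ICU and hospital length of stay, and mortality will also be noted".

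**Analyses.** The composite is built again from recorded variables: perioperative infarction, prolonged low output, prolonged vasoplegia, and any VT or VF episode in the first 24 hours. Low output is derived from two or more inotropes at 24 hours, or from use of IABC, ECMO or another assist device. The 24-hour condition is attached to the inotropes only. Death is again absent.

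On the model: "The raw effect of each type of cardioplegia on the acute cardiovascular event will be estimated using a logistic regression model". The intention-to-treat population keeps every randomized subject.

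**The concern.** A criterion that asks for support at or beyond 24 hours can be met only by someone alive at 24 hours. Death before then removes the chance to qualify, and death itself is not an event. In a superiority trial of myocardial protection, an early pump-failure death is the clearest clinical failure, yet it can be scored the same as an uneventful recovery.

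The direction of the error is what matters. Each such death lowers the observed event rate of its own arm, so an arm with more of them looks better on the primary outcome.

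The other main variable does not close the gap. Maximum troponin is taken from ICU arrival to 48 hours. A death in theatre gives no value, and a death a few hours later cuts the maximum short.

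**Working it through.** **1. The two definitions side by side.** Each row is a patient dying of pump failure.

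| Course | Outcome Measures | Analyses |
|---|---|---|
| Dies before 24 h, inotropes only, no MI, no VT/VF | no component met | no component met |
| Dies before 24 h on IABC or ECMO, no MI, no VT/VF | no component met (support must run past 24 h) | event (no time limit on devices) |
| Dies before 24 h, MI recorded | event | event |
| Dies before 24 h, VT/VF cardioverted | event | event |
| Dies before 24 h, VT/VF not cardioverted, inotropes only | no component met | event (any episode) |
| Dies after 24 h, still on two or more inotropes or a device | event | event |

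The first row is a gap under both definitions. The second and fifth rows are scored differently by the two. Prolonged vasoplegia (Analyses only) is not defined in the article, so it cannot be relied on to fill the gap.

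**2. The plan's own sample size.** Inputs from Sample Size Calculation: 38% v 25%, two-sided α 5%, power 80%, Fleiss correction, 10% losses.
- Uncorrected n = [1.960·√(2·0.315·0.685) + 0.842·√(0.38·0.62 + 0.25·0.75)]² / 0.13² = (1.288 + 0.547)² / 0.0169 ≈ 199.2, so 200 per arm.
- Fleiss correction: (199.2/4)·[1 + √(1 + 4/(199.2·0.13))]² ≈ 214.4, so 215 per arm.
- Losses: 215 × 1.10 = 236.5, so 237 per arm and 474 in total, as stated.

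This N rests on inotropic support within 24 hours, not on the composite. Adding death to the composite leaves it unchanged.

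**3. How many patients.** Evaluable per arm: 474 × 0.9 / 2 ≈ 213. The documents give no early-death rate, so 0.5% to 2% per arm is an assumption for deaths that meet no other component.
- 213 × 0.005 = 1.1 and 213 × 0.02 = 4.3, so about 1 to 4 per arm.
- As a share of an arm's events: 1.3% to 5.3% if the composite rate were 38% (0.5/38 to 2/38), and 3.3% to 13.3% if it were 15% (0.5/15 to 2/15). Neither is a documented composite rate.

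**4. Effect on the comparison.** For illustration only, take 38% (control) v 25% (DNS) as composite rates with these deaths counted, then score the deaths as non-events. Power is for 213 per arm without continuity correction.

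| Uncounted deaths, control / DNS | Observed rates | Difference | Power |
|---|---|---|---|
| 0 / 0 | 38% v 25% | 13 points | 82.6% |
| 1% / 1% | 37% v 24% | 13 points | 83.2% |
| 2% / 2% | 36% v 23% | 13 points | 83.9% |
| 1% / 2% | 37% v 23% | 14 points | 88.6% |
| 0 / 2% | 38% v 23% | 15 points | 92.2% |
| 2% / 1% | 36% v 24% | 12 points | 77.3% |

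Equal deaths leave the risk difference alone. The odds ratio that the logistic model estimates barely moves: (0.25/0.75)/(0.38/0.62) = 0.544 becomes (0.23/0.77)/(0.36/0.64) = 0.531 at 2% in both arms. Unequal deaths shift the difference by the size of the imbalance, towards the arm with more deaths.

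**The case against.** A reader might infer that every early pump-failure death is scored event-free, even on ECMO. The documents do not support that. A recorded MI or a cardioverted arrhythmia makes the patient an event under both definitions, as does death after 24 hours while still on qualifying support. Under Analyses any device use counts whenever it occurred. The ECMO case is missed under Outcome Measures only.

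A reader might also infer that the trial would not notice excess early deaths. Mortality is recorded, adverse events are followed with outcome and causality, and a safety analysis is planned at about 50% randomized. These would bring an imbalance to light, but none of them corrects the primary estimate.

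The article does not say how a death before 24 hours is coded, and coding rules are commonly left to the SAP or full protocol. That stands for the troponin handling, which is offered here as an improvement and not as an omission. It carries less weight for the composite: the article lists the components twice and omits death both times, so the non-event coding follows from the definition unless another rule overrides it.

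Finally, numbers are likely to be low. Emergent and unstable patients are excluded, and nothing in the documents suggests a difference in early death between solutions. That stands and limits the size of the point. On the other side, the trial deliberately takes patients over 80, with ejection fraction below 30% and with long bypass times.

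**Conclusion.** The gap is real but narrow. Under both definitions a death before 24 hours on inotropes alone, with no recorded MI and no qualifying VT/VF, meets no component and can count as a non-event under intention to treat. Under Outcome Measures alone, the same holds for an early death on IABC or ECMO.

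Its size cannot be derived from the documents. On the assumed 0.5% to 2%, it concerns about 1 to 4 patients per arm. Material bias requires a difference between arms; a 1 to 2 point imbalance would move a 13-point difference by 1 to 2 points in favour of the arm with more deaths. This is a cheap improvement worth making, not a defect that invalidates the design.

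**What to change.** - Reconcile the composite in Outcome Measures and Analyses: the time limit on device support, the cardioversion requirement, and prolonged vasoplegia.
- Add all-cause death within 72 h of surgery, death in theatre included, as a component in both sections. 72 h is the longest window already in the composite. At minimum, state that any death before the 24 h assessment is scored as an event.
- Report each component separately by arm, so that a reader can see whether death drives the result.
- For maximum troponin, add a sensitivity analysis that gives deaths before 48 h the worst rank.

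**Cost.** No new data are needed, since mortality is recorded and follow-up runs to discharge, and N does not change. A few non-cardiac deaths will enter a composite meant to reflect myocardial protection; reporting by component shows how many. Because inclusion began in 2018 and this is a primary outcome in an approved trial, the change needs a documented amendment, dated before outcomes by arm are examined. If the interim safety analysis has already compared arms, the amendment should record who has seen it.

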Several retrospective studies have assessed the safety and efficacy of DNS in adults undergoing coronary revascularization, valve replacement, combined procedures, and cardiac reinterventions [6-8].

In 2017, a meta-analysis comparing the effects of DNS and conventional cardioplegia solutions in adult cardiac surgery was published [9]. It concluded that there were shorter aortic cross-clamp times, reduced cardiopulmonary bypass times, reduced need for mechanical ventilation, and shorter intensive care unit (ICU) lengths of stay for the DNS group. On the other hand, no significant differences were observed as far as the following were concerned: the evolution of cardiac enzymes, postoperative vasoactive needs, the appearance of atrial fibrillation, in-hospital lengths of stay, or mortality. DNS appeared to be noninferior in terms of myocardial protection, morbidity, and mortality. Nevertheless, the results are somewhat restricted due to the lack of randomized prospective studies in the analysis.

Recently, two prospective studies assessing the effects of DNS in adults have been published [10,11], yet their primary outcomes focused on myocardial protection indirectly or on biochemical data (ie, electrical activity, need for ventricular defibrillation after the release of the aortic cross-clamp, and troponin evolution after surgery). Light has yet to be shed on the clinical advantages of DNS in adult patients, including older patients and those with a history of ventricular dysfunction.

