### Statistical Analyses

#### Sample Size Calculation

The literature reviewed reflects a need for postoperative inotropic vasoactive support ranging from 35% to 40%. In the sample size calculation, we propose that better myocardial protection will be reflected in a lower need for electrical cardioversion, lower pharmacological inotropic or mechanical support, and a lower incidence of myocardial infarction.

For a hypothetical reduction of inotropic support within the first 24 postoperative hours from 38% to 25%, with an α risk of 5%, at a statistical power of 80% (β=.20), by bilateral test with application of the Fleiss correction factor, and estimating losses of 10%, 474 participants distributed into two groups will be necessary.

Participants will be assigned to groups by simple randomization of the sample, obtaining a computer sequence by Stata 16 (StataCorp). The computer distribution will assign 234 participants to the intervention group (DNS) and 240 participants to the control group (blood cardioplegia). When patients arrive at the theater, perfusionists will enroll participants.

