## Discussion

### Overview

This study is expected to expand knowledge of DNS in adult cardiac surgery. DNS is assumed to be beneficial in terms of myocardial protection, and it is expected to corroborate a reduction in VF after declamping the aorta and in the number of defibrillations. Also, it is presumed to result in a reduction in postoperative troponin levels and inotropic support for low cardiac output syndrome. Although it is not the main objective of the study, the trial will provide information regarding the benefits of DNS in high-risk subpopulations, such as elderly patients and those with longer periods of cross-clamping or low ventricular ejection fraction.

This study is particularly relevant as it will be the first to analyze the clinical effects of del Nido cardioplegia on the basis of direct myocardial protection parameters. Although the meta-analysis published in 2017 highlighted some clinical benefits in favor of del Nido cardioplegia, there was a fundamental limitation, which is that data collection was based on retrospective studies.

Further published prospective studies also failed to focus their primary objectives on the analysis of the possible clinical effects of del Nido cardioplegia. Ad et al analyzed the postoperative troponin peak and the need for electrical cardioversion after aortic cross-clamp release in a population of 89 patients; in addition to its small sample size, this study excluded high-risk patients over 80 years of age, and the data showed short aortic clamp times [10].

Sanetra et al analyzed troponin peak and electrical activity after aortic cross-clamp release in a population of 150 patients undergoing aortic valve replacement. All clinical outcomes detailed in the study were part of the secondary objectives. Likewise, they excluded from their analysis reoperated patients with ejection fractions under 30% or with coronary artery disease susceptible to percutaneous interventionism or surgery [11].

In light of the above studies, carrying out prospective studies based on primary clinical objectives with a larger sample, high-risk patients, and longer cardiopulmonary bypass times continues to be necessary [12]. We believe that our study addresses an important gap in the knowledge of del Nido cardioplegia in adult patient cardiac surgery and will be able to clarify the possible benefits of this method in a large population of patients undergoing these procedures.

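### The subgroup with bypass longer than 120 minutes is defined after randomisation by a variable that treatment may affect, so randomisation may not protect the comparison within it

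*Protocol article*

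**What the plan says.** Outcome Measures names four subgroup populations: patients over 80 years, patients with ejection fraction below 30%, patients having coronary artery bypass grafting, and "patients undergoing prolonged cardiopulmonary bypass (longer than 120 minutes"). The first two are known before surgery, and the third can be fixed by the planned procedure. The fourth is a duration observed during the operation.

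Five other statements bear on it:

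- Sample Size Calculation: "When patients arrive at the theater, perfusionists will enroll participants". Patients therefore enter the trial before bypass starts.
- Outcome Measures, secondary efficacy and safety variables: "Among the intraoperative variables, surgical times (ie, ischemia time and cardiopulmonary bypass times"). Bypass time is thus both a secondary variable and a subgroup criterion.
- Scientific Background and Explanation of Rationale, on a 2017 meta-analysis of DNS against conventional solutions: "It concluded that there were shorter aortic cross-clamp times, reduced cardiopulmonary bypass times". The same paragraph adds that "the results are somewhat restricted due to the lack of randomized prospective studies in the analysis".
- Study Procedures and Interventions: the control arm receives maintenance doses every 20 minutes. The DNS arm receives a single dose, with further doses only under stated conditions.
- Discussion, Overview: "the trial will provide information regarding the benefits of DNS in high-risk subpopulations". The examples there include longer cross-clamping, and the sentence opens by saying that this is not the main objective.

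The article gives no baseline definition of expected long bypass and no caveat on how to interpret this subgroup.

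**The concern.** A subgroup comparison keeps the benefit of randomisation when membership is settled before allocation, or at least cannot be altered by it. Here membership depends on what happens in theatre after the allocated solution is given. Suppose DNS shortens bypass. Some patients of middling complexity would then exceed 120 minutes under control but not under DNS, and the DNS patients still above the line would on average be the harder cases. The arms inside the subgroup would differ in prognosis even if the solution had no effect on any clinical event.

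What is at stake is the reading of one exploratory result. Prolonged bypass is a setting of particular interest to the authors: Strengths and Limitations presents the inclusion of long-bypass procedures as an asset. An apparent lack of benefit there, or apparent harm, could be partly an artefact of selection.

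**Working it through.** **What the documents settle.** Three facts can be read directly. Membership is observed after treatment starts. The defining variable is also listed as a secondary variable. There is reported, non-randomised evidence that treatment may move it. The plan gives no figure for this subgroup, so there is none to reproduce, and the total of 474 (234 DNS + 240 control) is not in question.

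**How large could the bias be?** The documents give no bypass-time distribution, no relation of complexity to events and no number of minutes saved. All the inputs below are assumptions for illustration.

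Model A: bypass time T = 110 + 30c + 20e − δ·(DNS), with c (case complexity) and e independent standard normal. The SD of T is √(30² + 20²) = 36.06 minutes. Event risk: logit(p) = −1.9 + b·c, with b = 0.5 or 0.8 and no DNS term, so the true odds ratio (OR) is 1.00.

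*Share above 120 minutes, δ = 10.*
- Control: 1 − Φ(10/36.06) = 1 − Φ(0.277) = 0.391
- DNS: 1 − Φ(20/36.06) = 1 − Φ(0.555) = 0.290

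*Mean complexity in the subgroup*, (30/36.06)·φ(z)/(1 − Φ(z)).
- Control: 0.832 × 0.384/0.391 = 0.82 SD
- DNS: 0.832 × 0.342/0.290 = 0.98 SD

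*Event risk in the subgroup*, the mean of p given T > 120, by numerical integration over c.
- b = 0.5: control 0.1897, DNS 0.2021. OR = (0.2021/0.7979)/(0.1897/0.8103) = 1.08
- b = 0.8: control 0.2378, DNS 0.2603. OR = (0.2603/0.7397)/(0.2378/0.7622) = 1.13

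The same steps for other values of δ:

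| DNS shortens bypass by | Control >120 min | DNS >120 min | Subgroup OR, b = 0.5 | Subgroup OR, b = 0.8 |
|---|---|---|---|---|
| 0 min | 39% | 39% | 1.00 | 1.00 |
| 5 min | 39% | 34% | 1.04 | 1.06 |
| 10 min | 39% | 29% | 1.08 | 1.13 |
| 20 min | 39% | 20% | 1.18 | 1.28 |

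At 10 minutes the complementary stratum (120 minutes or less) is also shifted, to 1.07–1.11 by the same integration, while the whole-trial OR stays at 1.00. Both strata can lean the same way with no overall effect.

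Model B, as a sensitivity check: control bypass time normal with mean 110–120 and SD 30–40 minutes; logit(p) = −0.6 + 0.02 per minute of latent duration above the mean, that is, odds multiplied by exp(0.2) = 1.22 per 10 minutes; no DNS effect on events. Simulation gives a subgroup OR of 1.00 with no shortening, 1.06–1.07 at 5 minutes, 1.14–1.15 at 10 and 1.31–1.35 at 20.

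**How does this compare with the noise?** Under Model A with δ = 10, the expected subgroup is 240 × 0.391 ≈ 94 control and 234 × 0.290 ≈ 68 DNS patients. For b = 0.5 the expected events are about 17.8 and 13.7, so SE(log OR) = √(1/17.8 + 1/76.0 + 1/13.7 + 1/54.1) = 0.40. The bias is ln(1.082)/0.401 = 0.20 SE, and a 95% interval centred on it runs from about 0.5 to 2.4. For b = 0.8 the SE is 0.37 and the bias 0.33 SE. A nominal 5% two-sided test then rejects about 5.4% to 6.2% of the time; at 20 minutes, about 6.6% to 9.5%.

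**The case against.** The best case on the other side has four parts.

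*The shortening is not the protocol's own claim.* A reader might infer that the protocol asserts that DNS shortens bypass, and hence that the arms in this subgroup are not comparable. The documents do not support that. The Introduction reports what a meta-analysis of retrospective studies concluded and states its limitation. The benefits expected in the Discussion (less fibrillation after declamping, fewer defibrillations, lower troponin, less inotropic support) do not include shorter bypass. Nor does the dosing section say that maintenance doses lengthen bypass. This stands: loss of comparability is conditional on an effect that may be absent.

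*The bias is small beside the imprecision.* This also stands under the assumed models: at 10 minutes it is a fifth to a third of a standard error. But sampling error is visible in the confidence interval and selection bias is not, so imprecision does not cure it.

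*The analysis is exploratory.* True. The Discussion says that subpopulations are not the main objective, and it refers to longer cross-clamping, a related duration but not the same one. This limits the importance of the point without removing it.

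*An article may leave subgroup detail to the analysis plan.* That would answer a complaint about interaction tests or multiplicity. A reader might infer that every subgroup will be tested separately at 5%, but the article does not say so and none of that is part of this point. It does not answer the definition itself, which the article fixes with a numerical cut-off and no caveat.

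**Conclusion.** The point holds in conditional form. One of four planned subgroups uses a post-randomisation variable that is also a secondary variable and that treatment may affect. If DNS changes bypass time, randomisation no longer protects the comparison within that subgroup and the estimate can be biased; if it does not, the models above give no bias.

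The figure of about 1.1 for a 10-minute shortening rests wholly on assumed values for the bypass-time distribution, the complexity effect and the minutes saved. It shows what is possible and does not estimate what will occur. It would also be too strong to infer that the subgroup will make DNS look worse: that direction follows from an assumed uniform shortening, and a lengthening would reverse it. The primary analysis and the three other subgroups are untouched, the grafting subgroup provided that it is defined by the planned procedure. This is a modest flaw in an exploratory analysis, worth correcting because correction is cheap.

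**What to change.** Define the fourth subgroup by a feature recorded before randomisation, such as planned procedure type (for example combined, multiple-valve or redo surgery against an isolated procedure) or another baseline measure of complexity. Keep bypass and cross-clamp times as outcomes, compared between the full randomised arms.

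If the sponsor wishes to keep the 120-minute analysis because that threshold is of clinical interest, label it descriptive and non-causal, and report the number of patients in each arm who exceed 120 minutes so that readers can see whether membership differs.

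The cost is a change of wording before the data are analysed; no patients are added, and the planned procedure is known before surgery. The one real downside is that a baseline definition answers a slightly different question and does not map exactly onto bypass longer than 120 minutes.
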